**Eligibility flow diagram showing DoD chart abstractions using the Department of Defense Trauma Registry (DoDTR).**

### Study procedures

The VAVIS protocol was reviewed and approved by the VA Central IRB. This three component study will begin first by compiling data previously collected from DoD and VA (FY01-FY14), linking files from each source using the unique identifier. Once VA patients in the confirmed IILS cohort are identified, we will conduct medical chart abstraction of VA electronic medical records, and conduct a patient interview and survey to obtain patient reported outcomes. The study will start on April 1, 2015 and will be open for three years.

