The primary survey outcome measure for this study is one used for the GWOT VI: the *Short Musculoskeletal Function Assessment*. Additional instruments include the Paffenbarger Physical Activity Questionnaire, Chronic Pain Grade Scale, and the Military to Civilian Questionnaire MC2-Q (a measure of community re-integration). *Short Musculoskeletal Function Assessment* (SMFA) is a validated, 46-item self-reported health status questionnaire on extremity functional status. The SMFA contains two parts: the dysfunction index and the quality-of-life limitation index. The SMFA questionnaire has excellent internal consistency and stability, with most values greater than 0.90. Content validity for the dysfunction and bother indexes was supported with few ceiling effects (less than 5 percent), and no floor effects. Moreover, significant correlations were found between the SMFA dysfunction and other indexes and the physicians’ ratings of patient function (*e.g*., recreational and leisure activities, activities of daily living, and emotional function [rho ≥ 0.40]) and clinical measures including grip strength and walking speed [rho ≥ 0.40] [41].

*The Paffenbarger Physical Activity Questionnaire*
[42] (PPAQ) is a validated scale that describes participation in physical activity more specific to sports and leisure which has been used in a number of prior studies including the METALS study [11]. This instrument asks respondents to identify up to 4 activities performed in the past three months, the amount of time spent in those activities, and the intensity of those activities. This instrument allows a calculation of the approximate metabolic equivalents (METS) expended (e.g. an adult sitting quietly expends 1 MET). We will use Ainsworth’s Compendium of Physical Activities [43] to classify reported activity by the rate of expended energy into METS in the same manner used by the METALS study to improve comparability to findings.

*The Chronic Pain Grade (CPG) scale*
[44] is a validated measure of the severity of chronic pain. Similar to the METALS study, we will use the pain interference questions to distinguish the extent to which physical function and activities of daily living are affected by the pain [11].

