*The SF-8™* is the first SF survey to be constructed on the basis of empirical studies linking each questionnaire item to a comprehensive “pool” of widely used questionnaire items, including but not limited to the SF-36®, proven to measure the same health concepts. Because the item “pool” for each of the eight health concepts was calibrated on the same metric as the corresponding SF-36® Health Survey scale, each SF-8™ single-item scale and the SF-8™ summary measures can be scored on the same norm-based metrics as the SF-36® scales and summary measures. Thus, the SF-8™ is an 8-item version of the SF-36® that yields a comparable 8-dimension health profile and comparable estimates of summary scores for the physical and mental components of health [45]. Therefore, we will use the SF-8™ rather than the SF-36™.

The Military to Civilian Questionnaire is a validated, 16 item self-reported measure of experiences during military to civilian transition, developed by Sayer and colleagues at the Minneapolis VA/Polytrauma Center [46]. It was validated using a, stratified sample of 1,226 Iraq and Afghanistan Veterans who used VA medical care. The internal consistency of the M2C-Q was .95 in this sample. Factor analyses indicated a single total score was the best-fitting model. Total scores were associated with measures theoretically related to reintegration difficulties including perception of overall difficulty readjusting back into civilian life (R^2^ = .49), probable PTSD, probable problem drug or alcohol use, and overall mental health. Subgroup analyses revealed a similar pattern of findings in those who screened negative for PTSD.

In addition to these outcome variables, we will collect self-reported behavioral health symptoms.

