Depression Severity will be assessed with the Center for Epidemiologic Studies Short Depression Scale (CES-D 10), which has been demonstrated to be a valid and reliable measure to assess depression in both VA and non-VA settings [47–49]. The 10 items are rated on a 0 (rarely or none of the time) to 3 (all of the time) scale. Items for this instrument have not been directly mapped onto the 9 DSM IV diagnostic criteria for Major Depression, but the sensitivity and specificity average 80% and 70% respectively with regard to results from a formal diagnostic interview [47, 48]. PTSD Severity will be assessed with the PTSD Checklist-Military (PCL-M) [50]. The PTSD Checklist is a 17-item self-report measure designed to assess the diagnostic criteria of re-experiencing, avoidance and numbing, and hyperarousal. Respondents indicate on a 5-point scale (“Not at all” to “A great deal”) how much they were bothered by each symptom in the past month.

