To address the third aim (Describe patient-reported functional outcomes in Veterans with traumatic vascular limb injuries) we will begin by examining descriptive statistics associated with SMFA, PPFA, CPG scale, SF-8™, and M2C-Q). We will compare scores on these instrument among IILS patients with and without indicators of persistent morbidity, controlling for possible confounders associated with having indicators of persistent morbidity (from Aim 1) including CES-D, and PCL-M. We will then conduct separate generalized estimation equation analyses for each outcome, modeling the mean of each outcome as a linear function of the indicator of having one or more indicators of persistent morbidity and other covariates [52].

Secondary analyses will stratify individuals by initial injury severity type (e.g., vascular only, vascular + orthopaedic, vascular + orthopaedic + nerve, etc.) to further control for initial conditions that may be more difficult to control for in multivariable analyses. We will also examine the role of various prosthetic devices, including the extent to which the technology of the device, the number of different prosthetic devices per limb, etc. mediate the relationship between injury severity, persistent morbidity and functional outcomes. Furthermore, we will conduct generalizability analysis (described above) to examine whether the outcome model derived from the VA patients can be generalized to the non-VA patients.

Our power analysis for the third aim is based on the primary outcome: SMFA. Based on preliminary data, we assume that the proportion of patients with persistent morbidity falls between 10% and 50%. We also assume that the effect size associated with persistent morbidity on SMFA, PPFA, CPG scale, SF-8™, and M2C-Q no less than 0.435. Under those conditions, the study will have >0.80 power to identify a true difference in outcomes among those with and without persistent morbidity.

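### Aim 3 adjusts for current depression and PTSD scores as if they were only confounders, so the adjusted difference cannot be read as the total difference associated with persistent morbidity

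*Protocol article*

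**What the plan says.** All places are in the protocol article.

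- **Adjustment set.** The Analytic plan's third aim (the fourth in the section on the aims of VAVIS) compares SMFA, physical activity, CPG, SF-8 and M2C-Q scores by persistent-morbidity status, "controlling for possible confounders associated with having indicators of persistent morbidity (from Aim 1) including CES-D, and PCL-M". The regression that follows is described as "modeling the mean of each outcome as a linear function of the indicator of having one or more indicators of persistent morbidity" plus other covariates. No model without the two scores is named.
- **Timing of the scores.** Survey data introduces them right after the outcome instruments: "In addition to these outcome variables, we will collect self-reported behavioral health symptoms". PCL-M asks "how much they were bothered by each symptom in the past month".
- **Timing of the exposure.** The indicators are taken from Aim 1 and defined in Table 3 from care, pharmacy, device and pain-score records. Study procedures dates the compiled files FY01-FY14, and the study opens in April 2015.
- **Content of the outcomes.** The SF-8 yields "comparable estimates of summary scores for the physical and mental components of health". M2C-Q totals were associated with "probable PTSD, probable problem drug or alcohol use, and overall mental health". SMFA indexes correlated with physicians' ratings of domains such as "recreational and leisure activities, activities of daily living, and emotional function".
- **Reason for adjusting.** The aims section and the Figure 1 caption name psychiatric disease burden and mental comorbidity among the factors to be controlled.

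**The concern.** A confounder must act before, or independently of, the exposure. CES-D and PCL-M are measured after the morbidity indicators and together with the outcome. Some indicators in Table 3 (repeat procedures on the limb, mean pain above 4, long-term opioid use) could plausibly lead to current distress. The article itself remarks that repeated salvage surgery ending in limb loss can be demoralizing. If part of the burden of morbidity runs through mood and PTSD symptoms, holding those symptoms constant removes that part. Where the outcome itself contains mental health, adjustment also removes some of the outcome.

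At stake is what Aim 3 can conclude. The planned coefficient says how much worse Veterans with morbidity fare among Veterans with equal current symptoms. A reader will probably take it as how much worse they fare altogether.

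**Working it through.** **1. Order of measurement.** Exposure: records, with database files ending in FY14. Outcomes, CES-D and PCL-M: one survey, fielded from 2015. The scores are therefore post-exposure and concurrent with the outcome. No rule separates earlier psychiatric illness from current symptoms.

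**2. The plan's own figure.** The Analytic plan states power above 0.80 for an effect size of at least 0.435 with 10% to 50% prevalence of morbidity. It gives no survey N and does not say whether 0.435 is adjusted. Assuming SD 1 and two-sided alpha 0.05, power of 0.80 needs 462 respondents in total at 10% prevalence and 166 at 50%. At N = 700, the estimated VA cohort, power at 10% is 0.93. The claim is attainable, but it cannot be strictly reproduced or refuted.

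**3. Pure mediation.** Let *a* be the effect of morbidity on the symptom score (SD) and *r* the within-group correlation of the score with the outcome. Adjusted effect = 0.435 − *a·r*. The residual SD becomes √(1 − r²)/√(1 − ρ²), where ρ² = a²p(1−p)/(1 + a²p(1−p)) and p is prevalence. Both *a* and *r* are assumptions. Power is at N = 461, where the unadjusted comparison has 0.80 power at p = 10%.

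| a | r | Adjusted effect | Lost (a·r/0.435) | Power, p = 10% |
|---|---|---|---|---|
| 0 | 0.3 to 0.6 | 0.435 | 0% | 0.836 to 0.939 |
| 0.2 | 0.3 | 0.375 | 14% | 0.715 |
| 0.3 | 0.5 | 0.285 | 34% | 0.560 |
| 0.5 | 0.5 | 0.185 | 57% | 0.275 |
| 0.5 | 0.6 | 0.135 | 69% | 0.188 |

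The first row matters: if morbidity does not affect the scores, adjustment costs nothing and gains precision.

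**4. Mediation with confounding.** Simulation of 1,000,000 subjects with earlier mental health U (standard normal):

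- morbidity X: logit = −0.8 + u_x·U
- current score: M = 0.7U + a·X + 0.7·noise
- outcome: Y = (0.435 − a·b)X + b·M + u_y·U + noise

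The true total effect is 0.435 throughout, on the scale of the simulated outcome.

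| Setting (a, b, u_x, u_y) | Unadjusted | Adjusted for current score | Adjusted for earlier mental health |
|---|---|---|---|
| Pure mediator (0.4, 0.5, 0, 0) | 0.436 | 0.235 | 0.436 |
| Mediator and confounding (0.4, 0.5, 0.8, 0.3) | 0.894 | 0.263 | 0.432 |
| Proxy for confounder only (0, 0.5, 0.8, 0.3) | 0.898 | 0.548 | 0.436 |
| Weak mediation, strong confounding (0.4, 0.2, 0.8, 0.5) | 0.886 | 0.405 | 0.434 |

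Adjusting for the current score can give too little, too much or nearly the right answer. Adjusting for earlier mental health works in all four, but here it is measured perfectly, which diagnosis codes will not achieve.

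**The case against.** The strongest reply is that the protocol has a sound reason to adjust. Combat-related PTSD or depression may precede late morbidity, raise care-seeking, opioid use and pain scores (all Table 3 indicators), and worsen self-report. A score taken late can still reflect illness that began early. This stands. In three of the four simulated settings, leaving mental health out roughly doubles the effect.

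The aim is also worded as descriptive, and mental-health control is announced, so a conditional difference may be partly what is wanted. That is fair, but it then needs to be labelled as such. The regression sentence lists only other covariates, and its full specification may lie elsewhere. However, the comparison sentence just before it fixes the two scores by name.

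A reader might infer more than the documents support:

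- **That the effect is under-estimated.** No stated correlation or path fixes the direction, and 0.548 against 0.435 shows that it can reverse.
- **That the SMFA shares items with CES-D or PCL-M.** The article reports only correlations with physicians' ratings, one domain being emotional function. The overlap case is weakest for this primary survey outcome. For the M2C-Q, the article adds that the pattern was similar in those screening negative for PTSD, so its total is not merely a PTSD measure.
- **That the earlier military limb-trauma study shows morbidity causing PTSD.** It compared amputation with limb salvage, cross-sectionally, and not patients with and without persistent morbidity.
- **That the power statement is wrong.** Step 2 does not show this.

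**Conclusion.** The concern holds in a limited form. CES-D and PCL-M are post-exposure scores, concurrent with the outcomes, that the plan treats only as confounders. The adjusted difference is therefore conditional on current symptoms and is not the total difference associated with morbidity. The problem is clearest for the SF-8 mental component and the M2C-Q.

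Adjustment may under-estimate the difference to the extent that the scores result from morbidity, and it is legitimate to the extent that they reflect earlier mental illness. The net direction and size are unknown. The loss of 14% to 69% assumes *a* = 0.2 to 0.5, *r* = 0.3 to 0.6, no confounding, and 0.435 read as a total effect in SD units. None of these is given in the documents.

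**What to change.** For each Aim 3 outcome, pre-specify two models and report them side by side:

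1. Persistent morbidity, injury characteristics, TBI and mental-health diagnoses coded in the VA files at a common early date, for example at or soon after VA entry; without survey-time CES-D and PCL-M.
2. The same model plus CES-D and PCL-M, labelled as a difference conditional on current symptoms and not as the total effect of morbidity.

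The date must be common to both groups, because a window ending at the first morbidity indicator has no counterpart in patients without one. Table 2 supplies visit-level ICD-9-CM codes from VA care files; Table 1 lists no psychiatric diagnoses from the DoD abstraction, so the covariate has to come from VA data.

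The cost is one extra model per outcome and the work of building the covariate. Model 1 will keep some confounding by earlier mental illness that was not coded. A gap between the two models would not show by itself whether mediation or confounding caused it, and the report should say so.

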**Figure 1 Fig1:**
[figure not shown]
**Donabedian’s model of quality of care posits that processes of care (Vascular Preventive Care) may be associated with patient outcomes.** However, the complex relationships among demographic characteristics, initial injury severity, and comorbid physical and psychiatric conditions require careful attention to the potential for confounding and effect modifiers. While it is also important to control for demographic characteristics, particular concern is focused on controlling for disease burden and initial injury characteristics since these may have substantial impact on the outcome that is unrelated to the initial vascular injury and preventive care.

Because little is known about the natural history of these types of injuries given modern combat casualty care, our first aim is to describe the population of interest including initial and subsequent treatment in the DoD. Our second aim is to describe extant preventive care processes provided for individuals with IILS by the VA since best practices for individuals with traumatic vascular repair have not been established and little is known about the types of preventive care available. Because research in other types of care have found that processes of care identified as best practices are associated with patient outcomes [35], our third aim is to identify the association of Vascular Preventive Care with patient outcomes [36] such as measures of persistent morbidity, adjusting for potential confounders, and effect modifiers. While it is also important to control for demographic characteristics, particular concern will be focused on controlling for traumatic brain injury, physical and psychiatric disease burden, and initial injury characteristics since these may have substantial impact on the outcome that is unrelated to the initial vascular injury and preventive care [37]. If Vascular Preventive Care processes are associated with positive patient outcomes, there will be support for these care processes as best practices [38].

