**Table 3 Tab3:** **Indicators of persistent morbidity**

Indicators of persistent morbidity	Data used to identify	Data source
Use of unscheduled or emergency care for vascular issues	DSS Clinic Identifier and ICD-9 Codes	Outpatient (OPC) files; VA-CMS
Use of scheduled care for polytrauma vascular issues	DSS Clinic Identifier and ICD-9 Codes	OPC files; VA-CMS
Long-term use/escalating dose of opioid medications	VA Product, Dose, Day Supply	Pharmacy Benefits Management (PBM) Data; Medicare Part D VA-CMS
	NDC Code	
Trajectory of chronic pain (latent class analysis of pain scores from TRACC)	Pain Score	CDW vitals
Conditions indicative of persistent morbidity (e.g., Venous stasis disease/venous ulcers, lymphedema)	ICD-9 Codes including but not limited to 729.81, 782.3, 729.5, 415.19, 451.11, 451.19 451.83, 451.82, V72.83	PTF, OPC files, VA-CMS
Prescriptions for compression stockings and wound care supplies (e.g., wound vac) indicative of swelling, venous stasis disease	VA Class	PBM Data, VA-CMS Durable Medical Equipment
	XA	
Use of prosthetic/orthotic devices (canes, walkers, special shoes, etc).	Health Care Financing Administration Coding System (HCPCS) Prosthetic and Sensory Aids Service (PSAS) Code;	National Prosthetics database
		CMS Durable Medical Equipment
Additional procedures (open or endovascular) on the injured extremity	CPT-4; ICD-9A procedure codes	OPC/PTF VA-CMS
Chronic antibody use (osteo or other potential infectious issues with the limb)	VA Product	PBM Data; Medicare Part D VA-CMS
Duplex ultrasound, MRA/CTA or angiogram to evaluate the repair	CPT-4 procedure codes including but not limited to 93970, 93971, 93975, 93976, 93978, 93979, 93922, 93923, 93925, 93926, 93930, 93931, 93924	OPC/PTF; VA-CMS
Mean pain scores over 4	Pain Score Mean per year	Corporate data warehouse Vital Signs
Proportion of VA care	Visits VA/ Total Visits	OPC/PTF; VA CMS outpatient/inpatient
Mortality	Date of Death	VA Vital Status file

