To address the second aim, characterize the preventive services received by individuals with vascular repair and related outcomes, we will first compute the proportion of patients who receive antiplatelet agents, statins, annual duplex ultrasound, and vascular specialty care (and categories described above), and the percent patency each year for individuals without amputation. We will then examine the relationship between percent patency and preventive care using random effects analyses that models the vascular repair patency as a linear function of the indicator of receiving antiplatelet agents, statins, duplex ultrasound [51, 52], and other covariates/confounders (e.g., number of limbs affected, any initial, early or late amputations, mental health comorbidity, TBI diagnosis, and pre-existing chronic disease states such as atherosclerosis, diabetes, peptic ulcer disease), where the random effect is used to adjust for the within facility correlation, and the inverse of the propensity score for receiving antiplatelet agents/statins/yearly duplex ultrasound is adjusted for as weights. The adjustment of the propensity score for receiving antiplatelet agents/statins/yearly duplex ultrasound will minimize the estimation biases due to confounding by indication. We will also create different cut points (e.g. 75%, 50% patent), and use a binary outcome model. If Vascular Preventive Care processes are associated with positive patient outcomes, there will be support for these care processes as best practices.

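### As labelled, Table 3 lets routine duplex surveillance and scheduled vascular care count as persistent morbidity in the third-aim exposure, which also overlaps with the planned device mediator and the pain outcome

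*Protocol article*

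**What the plan says.** The Analytic plan's third aim models the mean of each patient-reported outcome on "the indicator of having one or more indicators of persistent morbidity" and other covariates. It names no rows, exclusions or weights.

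Table 3 is titled "Indicators of persistent morbidity" and repeats that phrase as its column heading. Its 13 rows include "Duplex ultrasound, MRA/CTA or angiogram to evaluate the repair", "Use of scheduled care for polytrauma vascular issues", "Use of prosthetic/orthotic devices (canes, walkers, special shoes, etc", two rows built from clinic pain scores, the proportion of care received in the VA, and mortality. The section on previously collected data, which introduces the table, says it describes morbidity indicators, type of care received and long-term outcomes. No row is marked as belonging to one of these families.

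For the second aim, the Analytic plan computes "the proportion of patients who receive antiplatelet agents, statins, annual duplex ultrasound, and vascular specialty care" as preventive services. The Aims section numbers its aims differently and says "our third aim is to identify the association of Vascular Preventive Care with patient outcomes", giving measures of persistent morbidity as an example of those outcomes.

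A secondary analysis asks how far prosthetic devices, through their technology and number per limb, "mediate the relationship between injury severity, persistent morbidity and functional outcomes".

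**The concern.** One binary exposure carries the comparison for every patient-reported outcome, including the SMFA. If it mixes ill health with receipt of routine follow-up, the contrast no longer compares patients with and without persistent morbidity. Patients under good surveillance move into the morbid group and, if they function well, pull its mean towards that of the comparison group.

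The overlap also touches the protocol's argument about best practice. The article says favourable associations between preventive care and outcomes would support those processes as best practice. If a duplex scan is both the care received and a marker of the bad outcome, the shared component pushes the association towards care going with morbidity, whatever the care achieves. Covariate adjustment or propensity weighting cannot remove a component that sits in both variables by definition.

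**Working it through.** **1. The definitions side by side**

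| Item | Role elsewhere in the plan | Role in Table 3 |
|---|---|---|
| Duplex ultrasound | Preventive service (second aim), CPT-4 codes in Table 2 | Morbidity indicator, CPT-4 codes |
| Vascular clinic care | Preventive service (second aim), clinic stop codes in Table 2 | Scheduled vascular care as morbidity indicator, clinic identifier plus ICD-9 |
| Prosthetic devices | Mediator: technology and number per limb | Any device use as morbidity indicator |
| Pain | Outcome: Chronic Pain Grade | Mean score over 4 and pain trajectory as morbidity indicators |
| Share of care in the VA | None in the third-aim models | Morbidity indicator, no threshold given |
| Death | Cannot be observed in a survey respondent | Morbidity indicator |

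The imaging row refers to evaluating the repair, but surveillance scans also evaluate the repair, and the row is identified by procedure codes alone. No rule separates routine from symptom-driven tests. MRA/CTA and angiogram are not second-aim services, so the overlap with preventive care concerns duplex and vascular clinic care only.

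Under a one-or-more rule that includes the device row, every device user is exposed and no unexposed patient can have a device. The mediator can then vary only within the exposed group.

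**2. The plan's own power statement**

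Inputs: effect size 0.435, morbidity prevalence 10% to 50%, power above 0.80. Two-sided alpha 0.05 is assumed. The article gives no survey N for this aim; 700 is the estimated VA denominator for the database and chart components.

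Power = Φ(d·√(N·p·(1−p)) − 1.96); N for 0.80 power = (1.96 + 0.84)² / (p·(1−p)·d²).

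- p = 10%: N ≈ 461. p = 50%: N ≈ 166.
- N = 700, p = 10%: 0.435 × √63 − 1.96 = 1.49, power 0.93. At p = 50%, power exceeds 0.99.

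So the claim is attainable if about 461 of 700 (66%) supply survey data. It cannot be confirmed or refuted from the article.

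**3. Direction and possible size of dilution (illustration only)**

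Suppose a share x of the flagged group is flagged only by surveillance or scheduled care and functions like the unflagged. Then d becomes 0.435 × (1 − x). With x = 30%, d = 0.30:

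| Flagged share | Power, N = 700 | Power, N = 461 |
|---|---|---|
| 10% | 0.68 | 0.50 |
| 50% | 0.98 | 0.91 |
| 75% | 0.94 | 0.81 |

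Alternatively, let m be true morbidity and c the share with a care or imaging flag, independent of m. The flagged share is P = m + c − mc and the diluted effect is 0.435 × m/P. At N = 700:

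- m = 10%, c = 20%: P = 28%, d = 0.155, power 0.45.
- m = 30%, c = 44.7%: P = 61%, d = 0.213, power 0.78.
- m = 50%, c = 44.7%: P = 72%, d = 0.301, power 0.95.

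The 44.7% is borrowed from the second-aim ceiling for antiplatelets, statins or yearly duplex; it is not a documented rate for these two rows. The values of x, m and c and the independence are assumptions. The effect size always falls, but the power consequence runs from negligible to large.

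**The case against.** The strongest reply is that the text introducing Table 3 announces three families of measures. Imaging, scheduled care and VA share fit type of care, and mortality fits long-term outcomes. The third-aim text does not cite Table 3, and the first-aim list of morbidity indicators is narrower: frequent or emergency vascular care, venous stasis disease, prosthetic use and long-term opioids. On this reading the authors never meant a routine scan to count, and exact row assignment belongs in the full plan.

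This stands as far as intent goes. It does not remove the fault, because the title and column heading give every row the same label, no row is assigned to another family, and the first-aim list is given only as examples. A programmer working from the article would include all rows.

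A reader might infer more than the documents support:

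- *That the care–morbidity association will be positive by construction.* The Analytic plan specifies no regression of morbidity on care; its second-aim outcome is patency. The association appears only in the Aims section, and antiplatelets and statins are not in Table 3. Duplex on both sides biases such an analysis upward but does not fix its sign.
- *That the mediation estimate is meaningless.* The mediator is device technology and number, while Table 3 records any use. The analysis is partly circular, and it is secondary.
- *That the pain result is a tautology.* The Chronic Pain Grade is used through its interference questions, which overlap with clinic pain scores but are not identical to them. It is not the primary survey outcome.
- *That the study is underpowered.* The power loss in the first illustration arises at 10% flagged with an assumed 30% dilution; at 50% or 75% flagged, power stays above 0.80. Nor does the article say whether 0.435 refers to an indicator with or without the care rows.

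**Conclusion.** The point holds as a fault of definition. Taken literally, the third-aim exposure classes recipients of routine duplex or scheduled vascular care as morbid, contradicting their role as preventive services in the second aim. It contains device use while device features are the mediator, and pain scores while pain interference is an outcome. The likely effect on the SMFA contrast is attenuation, provided that patients flagged only by care function like those not flagged; the article offers no figure from which to compute its size. The conclusion rests on the wording of Table 3 and the Analytic plan, not on the illustrative power figures. It should be settled before outcomes are analysed, because choosing rows afterwards would be post hoc.

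**What to change.** - Mark each Table 3 row as morbidity, care process/utilisation (duplex/MRA/CTA/angiogram, scheduled vascular care, proportion of VA care) or long-term outcome (mortality).
- State that the third-aim indicator uses the morbidity rows only, and name them.
- Leave device use out of the indicator in the device mediation analysis.
- When the outcome is the Chronic Pain Grade, leave the pain-score rows out, at least as a sensitivity analysis.
- Check that the 10% to 50% prevalence and the 0.435 effect size refer to the indicator so defined, and revise the power statement if they do not.

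The cost is a relabelled table and a short paragraph, with no change in data collection. The downside is fewer flagged patients, which matters most if prevalence is near the 10% end, where about 461 respondents are needed for 0.80 power.
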